### Plans to give access to the full protocol, participant level-data and statistical code {31c}

Upon publication of the planned research papers, we intend to share the de-identified data for future research purposes upon reasonable requests.

## Oversight and monitoring

### Composition of the coordinating centre and trial steering committee {5d}

The national principal investigator and her deputy will lead the study. The Institute for Medical Informatics, Biometry and Epidemiology/Center for Clinical Trials Essen is responsible for clinical project management, data management, monitoring and statistical analysis and acts as an independent scientific institution. The study will be monitored by the G-BA with regard to the applicable guidelines.

### Composition of the data monitoring committee, its role and reporting structure {21a}

To ensure patient safety, a Data Safety Monitoring Board (DSMB), consisting of three experts (radiologist, statistician, trauma surgeon), will supervise the study. This committee will hold biannual meetings and will monitor the progress of the study in terms of recruitment and conduct, evaluate the safety data based on interim analyses and provide recommendations to adjust the risk–benefit assessment.

### Adverse event reporting and harms {22}

(Serious) adverse events ((S)AEs) and (serious) adverse device effects ((S)ADEs) will be documented in the eCRF at each study visit or as soon as they become known to the investigator and reported to the ZKSE within 7 working days (AEs/ADEs) or 24 h (SAEs/SADEs) of becoming known. An ADE is defined as an AE related to the use of the ultrasound device and includes events resulting from inaccurate instructions, malfunction or user error. An SADE is defined as a defect that has resulted in any of the characteristics of an SAE, i.e., death, life-threatening, requiring hospitalization or prolonging an existing hospitalization, or resulting in prolonged significant disability or incapacity.

An incident is defined as a malfunction or deterioration in the characteristics or performance of the ultrasound device, including application errors due to ergonomic features, as well as an inadequacy of the information provided by the manufacturer or an undesirable side effect. Incidents do not include individual anatomical or physiological characteristics of the patient or human errors (e.g., due to the influence of alcohol or drugs, fatigue, lack of device instruction) that have led to a treatment problem without a defect or malfunction of a medical device. For the CE-certified ultrasound device that is already on the European Union market, any incident related to the device that is not an expected side effect, clearly documented in the product information, will be reported by the manufacturer to the Federal Institute for Drugs and Medical Devices via an incident report.

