**Fig. 2 Fig2:**
[figure not shown]
Trial schedule. *low-intensity pulsed ultrasound. **Numeric Rating Scale. ***Short Form-12. ****Disabilities of the Arm, Shoulder and Hand Questionnaire. *****Lower Extremity Functional Scale Questionnaire. ^a^If more than 4 weeks pass between screening and visit 0, the inclusion/exclusion criteria will be checked again and, at the discretion of the attending investigator, imaging will be repeated if necessary. ^b^X-ray/CT control for surgical planning (standard examination; may not be necessary if current imaging will be available that is sufficient for surgical planning. This will be at the discretion of the attending investigator). ^c^Postoperative complications that are attributable only to the surgery (e.g., wound infection) will be recorded accordingly only for the control group. ^d^Before starting the intervention, the correct location for LIPUS will be marked under X-ray control. ^e^If the bone is found to be consolidated (at least 3 out of 4 cortices will be radiologically confirmed to be consolidated) at visit 4, no further imaging will be performed unless this would be necessary at the investigator`s discretion. ^f^If full-weight bearing is possible, the time at which full weightbearing is reached will be documented

Visit 1 will take place as the first check-up 14 days after the start of the ultrasound treatment or after the operation. A physical examination will be carried out again and the range of motion, the weight-bearing capacity and the NRS will be documented. Patients will be asked about aids, supportive measures, medication taken, possible complications from the treatment and (serious) adverse events ((S)AEs) and (serious) adverse device effects ((S)ADEs) will be recorded.

Visits 2 to 4 will take place at around 6 weeks, 4 months and 6 months after baseline. Visit 5, which will take place 1 year after baseline, is the final visit. The dates correspond to the standard follow-up visits carried out during the treatment of non-unions. A physical examination will be carried out at all appointments, and the corresponding questionnaires will be given to the patient. All complications that will have occurred during treatment will be assessed. An X-ray or CT scan will be performed at the discretion of the investigator in accordance with routine treatment (Fig. 2).

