### Sample size {14}

Sample size estimation is based on a Z-test with non-pooled variances to verify the non-inferiority of treatment with LIPUS compared to surgical treatment. A fracture-healing rate of 86% is assumed in the surgical treatment group based on previous studies [6]. In the intervention group, a fracture healing rate of 75% is assumed [6, 9–14]. Since spontaneous healing, i.e. healing without treatment, only occurs in an estimated 5% of cases, it can be assumed that both treatments are superior to no treatment.

LIPUS treatment is assumed non-inferior to surgical treatment if the proportion of fracture healings in the intervention treatment group is less than 25 percentage points lower than in the control group. If a fracture-healing rate of 86% is assumed with surgical treatment and LIPUS treatment is actually non-inferior to surgical treatment, this means that fracture healing can be expected in more than 61% of those treated with LIPUS. In these, surgical intervention can be avoided and all the risks associated with it (e.g., re-hospitalization, secondary diseases or side effects of surgery such as infections and anesthetic incidents). Patients, whose fractures have not healed, will still be able to undergo surgical intervention at a later date. Assuming healing rates of 86% for surgical and 75% for LIPUS treatment, patients with incomplete fracture healing would be considered as treatment failures, included in the 14% or 25% unsuccessful treatment outcomes. Since no relevant side effects are to be expected from LIPUS treatment, the risk of delayed fracture-healing in the event of unsuccessful LIPUS treatment is therefore offset by the risk of unnecessary surgical intervention. The non-inferiority threshold of −25 percentage points is considered appropriate in this context.

With the above assumptions, a one-sided significance level of 2.5% and a power of 90%, 166 patients are required per group. In addition, a dropout rate of 10% is assumed. The proportion of dropouts of max. 10% appears realistic, as patients with non-unions require regular clinical and radiological check-ups (timed to coincide with the study visits) even without participating in the study. The intention-to-treat (ITT) analysis will be used to include patients who will not comply with the protocol. Based on the above assumptions, 184 patients will have to be recruited per treatment group. Accordingly, a total number of 370 cases will be required.

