## Statistical methods

### Statistical methods for primary and secondary outcomes {20a}

Treatment with LIPUS will be analyzed with a non-inferiority test against surgical treatment for the primary endpoint of fracture healing. A one-sided 97.5% confidence interval will be estimated for the difference in the proportion of fracture healing between the two groups. If the lower limit of the confidence interval will be greater than the non-inferiority limit of −25 percentage points, the null hypothesis of no non-inferiority will be rejected at the significance level α = 0.025. In addition, a generalized linear mixed model (GLMM) will be fitted to evaluate the robustness of the result for the binary endpoint of fracture healing. Treatment, sex, age and upper vs. lower limb will be considered as fixed effects. The study sites will be modeled as random effects. In order to estimate the risk difference for the treatment in the GLMM, the identity link will be considered as a link function for this endpoint. In addition, the analyses will be performed separately for radiographic bony consolidation and functional restoration. An intention-to-treat (ITT) analysis will be performed as well as a per-protocol (PP) analysis as a sensitivity analysis. The safety analysis will be based on the documented (S)AEs/(S)ADEs. All secondary endpoints will be analyzed exploratively, that is, without adjustment for multiple testing, using standard methods of statistical inference appropriate for the scale level of the endpoint in question. Scores for DASH and LEFS will be considered as continuous outcomes for which linear mixed regression models will be used, where sex, age, and upper or lower extremity will be included as fixed and study sites as random effects.

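### The definition of a serious adverse device effect requires a device defect, which contradicts the adjacent definition of an adverse device effect and may make the SADE count too low

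*Protocol article*

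**What the plan says.** Both definitions stand next to each other in Adverse event reporting and harms {22}.

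- For the ADE, the wording is: "is defined as an AE related to the use of the ultrasound device and includes events resulting from inaccurate instructions, malfunction or user error".
- The next sentence reads "An SADE is defined as a defect that has resulted in any of the characteristics of an SAE", followed by the usual list: death, threat to life, new or prolonged hospital stay, lasting disability or incapacity.

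The same section requires AEs, SAEs, ADEs and SADEs to be entered in the eCRF and "reported to the ZKSE within 7 working days (AEs/ADEs) or 24 h (SAEs/SADEs) of becoming known". It separately defines an incident. This covers device malfunction or deterioration, use errors arising from ergonomic features, inadequate manufacturer information and undesirable side effects. It excludes human error where the device had no defect or malfunction.

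On analysis, Statistical methods for primary and secondary outcomes {20a} says only: "The safety analysis will be based on the documented (S)AEs/(S)ADEs".

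**The concern.** The name says that an SADE is a serious ADE, but the definition does not. An ADE is an event in a patient, while a defect is a state of the device, so the two sentences do not describe the same kind of thing. The ADE sentence expressly "includes events resulting from inaccurate instructions, malfunction or user error", and at least user error can occur with a device that works perfectly.

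The route matters in this trial because patients apply LIPUS themselves at home, fixing the strap and placing the probe after training (Intervention description {11a}). Serious harm through misuse of a sound device is the case that the wording leaves out.

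What is at stake is a safety label. SAEs in either arm include events that have nothing to do with the device. The SADE class is the one that names serious harm attributed to it. If its entry rule is too narrow, the number reported under that name can be too low.

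**Working it through.** No arithmetic applies: the point depends on no rate, margin, error level or sample size, and the article gives no SADE figure to reproduce. The check is to take a serious, device-related event in the LIPUS arm and apply each definition in {22} as written, by cause.

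| Cause of the serious event | ADE | SAE | SADE as written | Incident |
|---|---|---|---|---|
| Device malfunction | yes | yes | yes | yes |
| Inaccurate instructions, device sound | yes | yes | no | yes, if the manufacturer's information was inadequate |
| User error, device sound | yes | yes | no | no, unless due to ergonomic features |
| Correct use, device sound | yes | yes | no | possibly, as an undesirable side effect |

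**ADE column.** Relation to use of the device is enough. Malfunction is one of three causes named, and no defect is required.

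**SAE column.** An ADE is by definition an AE. If it meets a seriousness criterion it is an SAE, whatever its cause.

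**SADE column.** Only the first row clearly involves a defect. Of the three causes named for ADEs, inaccurate instructions and user error need not involve one. One could stretch the word to cover faulty instructions, but it cannot reasonably cover user error. The incident paragraph of the same section contrasts human error with a defect or malfunction of the device, so within this section the word means a device fault.

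**What happens to an event in the last three rows.** It is entered in the eCRF as an SAE and an ADE. It falls under the 24 h limit as an SAE, the same limit that an SADE would have. It belongs to the documented events on which {20a} bases the safety analysis. Only the SADE label, and with it the SADE tally, is lost.

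**With the corrected definition.** All four rows become SADE = yes, and no other column changes.

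**The case against.** Three arguments can be made against the point.

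*It is a slip of the pen.* The label says effect and the definition says defect, and an investigator guided by the label would classify correctly. This is plausible, but it is inference. Sites apply the text they are given, and the neighbouring paragraph uses the word in its ordinary sense. A slip in an operative definition still needs correcting.

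*Nothing is lost.* This stands, and it limits the point. A reader might infer that serious device-related events without a defect go uncounted and that LIPUS harms are understated overall. The article does not support that: these events remain SAEs and ADEs, reach the trial centre within 24 h and enter the safety analysis. If the eCRF records seriousness and device relation on the same event, the correct count could even be rebuilt. The article does not say whether it does.

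*The margin is untouched.* This also stands. The sample size section argues for the −25-point margin partly on the premise "Since no relevant side effects are to be expected from LIPUS treatment", and a reader might infer that a narrow SADE definition shields that premise from being tested. But the premise is a planning assumption, and no test of it based on SADEs is specified. The class that can be compared across both arms is SAEs, and the SADE wording does not affect it. Nor does the article describe an SADE table for the analysis or for the DSMB, whose task is to evaluate the safety data generally.

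**Conclusion.** The definition is wrong as written, and the point is minor. The SADE sentence contradicts the ADE sentence beside it. Applied literally, it gives a wrong classification for any serious device-related event without a device fault, and the SADE count may then be too low.

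The size cannot be derived, because no event rate is stated. The abstract and Background and rationale {6a} describe skin reactions as the only side effect and as very rare. If that holds, few events would be affected.

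The conclusion assumes that sites follow the wording rather than the label, and that eCRF guidance not shown here does not already correct it. No change to the primary estimate, the margin, the error rate or the sample size follows.

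**What to change.** Replace the SADE sentence with: *An SADE is an ADE that meets at least one of the seriousness criteria for an SAE*, keeping the existing list of criteria. Align the eCRF completion guidance with it.

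No separate recording of device defects needs to be added, because the incident category already covers malfunctions. The cost is one sentence in the protocol and a matching line in the guidance, with no change to data collection, visits or analysis.

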### Frequency and plans for auditing trial conduct {23}

The investigators and institutions involved in the study allow study-related monitoring and audits by the G-BA. In the event of an audit, the investigator will agree to grant the auditor access to all study-related documents. This will also apply to all local or state authorities that are legitimized by applicable law.

### Plans for communicating important protocol amendments to relevant parties (e.g., trial participants, ethical committees) {25}

All changes to the protocol are submitted to the relevant ethics committees for approval and will be entered into the study registry. Already randomized patients will have to sign an updated informed consent form. All deviations from the protocol will be fully documented and tracked using breach reporting forms to ensure the transparency and integrity of the protocol.

### Dissemination plans {31a}

After completion of the study, the study management will submit the final report to all designated recipients within the applicable deadlines. The final report will be prepared in accordance with the ICH E3 guideline and the G-BA's specifications and will be submitted to the G-BA together with the statistical analysis plan. Publication of the results will be independent of the outcome. The results will be published in peer-reviewed international medical journals and presented at national and international conferences.

## Discussion

The aim of this G-BA-funded study is to prove that in patients with non-unions, treatment with low-intensity pulsed ultrasound is not inferior to surgical intervention in terms of the fracture healing rate endpoint (non-inferiority question). Despite medical advances, non-unions occur in approximately 2–10% of all fractures and can affect up to 30% if certain risk factors are involved [1, 2]. To date, surgical revision has been the gold standard in the treatment non-union, with the surgical procedure depending on the type of non-union. The disadvantages of surgical intervention are re-hospitalizations associated with the operation as well as possible secondary diseases and side effects such as postoperative infections, anesthetic incidents and embolisms. A possible alternative to surgical revision for non-unions is treatment with LIPUS, although this is currently considered an individual health service and the benefits over surgery have not yet been shown in a comparative study with sufficient certainty of results.

One of the strengths of our study lies in its design. The study will be conducted as an open, controlled and randomized study with 370 patients over 2 years at approximately 20 study sites. Blinding of patients and investigators is not possible due to the nature of the intervention. A possible bias will be significantly attenuated by the choice of an endpoint committee. To assess the primary endpoint (assessment of fracture healing), only the last available X-ray/CT image of the individual patients will be presented to the independent endpoint committee. This means that the assessor will not be able to draw any conclusions as to whether, for example, implants have been replaced, i.e. whether a surgery has taken place.

To improve the accuracy and reliability of the study, a approved and CE-marked ultrasound device will be used, which has been used for the treatment of non-unions for several years. Furthermore, the device allows compliance control in the implementation of the treatment for the individual patients. In addition, the SF-12, DASH and LEFS questionnaires are widely used and validated. If non-inferiority of LIPUS compared to standard therapy (surgical revision) is proven in this study, patients with non-unions will have a choice of both invasive and non-invasive/non-surgical therapy methods in the future. The costs for LIPUS treatment should also be covered by health insurance companies in the future if non-inferiority is proven. This would be particularly beneficial for patients with other pre-existing conditions and with an increased risk of anesthesia, as well as for patients who refuse surgery for other reasons.

## Data Availability

The Principal investigator, the Project Manager and Data Management will have full access to the data with a personal confidential password. The University Hospital Essen and the BG Klinikum Duisburg own all research data collected as part of this project. The principal investigator takes responsibility for all data collection, management, and sharing of research data. It will be possible to re-use the data for further research, document the validity of the research, and make possibilities for data sharing and collaborations upon reasonable request.

## Abbreviations

CT: Computer tomography
DASH: Disabilities of Arm, Shoulder and Hand Questionnaire
DSMB: Data Safety Monitoring Board
eCRF: Electronic Case Report Form
EDC: Electronic data capture
GCP: Good Clinical Practice
GLMM: Generalized linear mixed model
ICD-Code: International Statistical Classification of Diseases and Related Health Problems
ICH: International Council for Harmonization of Technical Requirements for Pharmaceuticals for Human Use
LEFS: Lower Extremity Functional Scale
LOCF: Last observation carried forward
MCID: Minimal Clinically Important Difference
LIPUS: Low-intensity pulsed ultrasound
NRS: Numerical Rating Scale
PROM: Patient Reported Outcome Measure
SF-12: Short-Form 12
(S)ADE: (Serious) Adverse Device Effect
(S)AE: (Serious) Adverse Event
ZKSE: Zentrum für klinische Studien Essen (Center for Clinical Trials in Essen)
